
#### Secondary outcomes

Surface electromyography: The surface electromyography signal is collected synchronously with the three-dimensional gait analysis system. The specific operation is as follows: ① On the wireless surface electromyography control terminal, select 8 muscles on both sides, including rectus femoris, biceps femoris, anterior tibial muscle, and gastrocnemius muscle; activate the wireless surface electromyography electrode; pair it with the control terminal through wireless wifi; and set the wireless channel of the relevant muscles in sequence. ② Place the common monitoring electrode at the thickest position of the abdomen of the relevant muscles of the lower limbs, parallel to the direction of the muscle fibers. Finally, install the surface electromyography electrode on the electrode piece. ③ Set the signal acquisition mode to “remote” mode. At the same time of three-dimensional gait analysis, the system will automatically record the original myoelectric signals of the relevant muscles synchronously, and automatically transmit the myoelectric data from the control end to the computer after the acquisition and save it to the database of three-dimensional gait analysis. The original surface EMG signal is processed by the righting and de-blurring provided by the software. The derived data include original data, root mean square amplitude (RMS), activation period (ACTI), integral EMG, and median frequency. The electromyographic signals were smoothed and filtered using Noraxon MR3 software, rectified and bandpass filtered (10–500 Hz). Data was exported to Excel and was time normalized. The data was calculated using Mat Lab 2020 software and Excel 2016 software.Isokinetic muscle strength test: Isokinetic muscle strength is measured on the peak moment of knee flexion and knee extension (Biodex™, USA) at the angular velocity of 30 degrees/s and 90 degrees/s.Lysholm score is a rating system in the evaluation of knee ligament injuries and is comprised of 8 tissues, of which the patient can achieve a maximum score of 100 [16]. The content includes limp (5 scores), support (5 scores), locking (15 scores), instability (25 scores), pain (25 scores), swelling (10 scores), stair-climbing (10 scores), and squatting (5 scores). Above 91 points is excellent; 84–90 points is good; 65–84 points is fair, and less than 65 points is poor.Thigh circumference is using a tape measure to measure the circumference of the thigh at 10 cm above the patella.

### Participant timeline {13}

This paper is written according to the Standard Protocol Items: Recommendations for Interventional Trials (SPIRIT) 2013 Statement for the reporting of clinical trial protocols (Table 3) [17].

**Table 3 Tab3:**
[figure not shown]
Standard Protocol Items: Recommendations for Interventional Trials (SPIRIT) figure showing the schedule of enrollment, interventions, and assessments

### Sample size {14}

Using the G Power 3.1.9.7 software, previous studies showed that between the proprioceptive training group and the comparator group, the effective amount of JPS joint position perception difference *d* = 0.97 [13]; According to power = 80%, alpha = 0.05, and *d* = 0.97, the required sample size *n* = 36 is calculated. Considering the loss of 10% sample size, 40 subjects are required.

### Recruitment {15}

Patients will be recruited at the Sports Medicine and Orthopedics of Zhongda Hospital Southeast University in Nanjing.

## Assignment of interventions: allocation

### Sequence generation {16a}

Use Excel to create sample size values, generate random numbers, copy and paste new units (only copy values), divide them into experimental group and comparator group.

### Concealment mechanism {16b}

Write numbers into envelopes according to the sequence and put them into kraft paper by researchers unrelated to this clinical trial. All personnel did not know the sequence details in the envelope.

### Implementation {16c}

When the subject was confirmed to be included in the group, the implementer opened the envelope in the office to determine whether to enter the test group or the comparator group.

## Assignment of interventions: blinding

### Who will be blinded {17a}

Because the implementers and patients of the proprioceptive training group and the conventional group can clearly observe; Therefore, the blind method of this study is only blind for the evaluators of outcome indicators and data analysts. Data collection and analysis shall be conducted independently by researchers who do not participate in the trial.

### Procedure for unblinding if needed {17b}

Because the blind method of this study is only blind for the evaluators of outcome indicators and data analysts, there is no need to unblind.

## Data collection and management {18a 18b 19}

### Plans for assessment and collection of outcomes {18a}

A non-intervention researcher will record the included patient information in the form of a spreadsheet, including baseline data and research data. Before the clinical research data collection, the data collection researcher shall be trained, and more than three times of data simulation records shall be completed to understand the definition of the outcomes.

### Plans to promote participant retention and complete follow-up {18b}

We will use an intention-to-treat (ITT) analysis. A study participant is analyzed as belonging to whatever treatment group he/she was allocated, whether or not the treatment course was completed as intended.

### Data management {19}

The information during the telephone follow-up will be recorded on paper, locked in the cabinet, and registered in the electronic form by the non-intervention researcher.

### Confidentiality {27}

Research data will be only available to the responsible researcher and co-authors. All data will be used for academic study and participant’s information details will not be reported in publications.

### Biological specimens {33}

N/A. This study does not have biological specimens.

## Statistical methods

### Statistical methods for primary and secondary outcomes {20a}

The data are presented as the mean ± standard deviation for normally distributed continuous variables and as proportions for categorical variables. The continuous variables were compared using Student’s *t*-test, and categorical variables using *χ*^2^ test. To analyze the effectiveness of the trial with change over time (from baseline to week 6 and week 12), repeated measures analysis of covariance (ANCOVA) will be applied, and treatment, time, and the treatment × time interaction as independent variables. The results are reported as mean ± SD and their 95% CIs and *P* values < 0.05 were considered statistically significant.

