### Trial design{8}

This trial is a single center, single-layer (the experimental group and the comparator group were randomly assigned in a 1:1 balanced manner), and the evaluator was blind.

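### The repeated measures ANCOVA names no covariate and no efficacy contrast, so the 80% power planned for a simple two-group comparison does not automatically carry over to it

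*Protocol article*

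**What the plan says.** All references are to the protocol article.

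- **Statistical methods {20a}.** To assess effectiveness over the span from baseline to weeks 6 and 12, "repeated measures analysis of covariance (ANCOVA) will be applied, and treatment, time, and the treatment" × time interaction are given as the independent variables. No covariate is named. The section does not say which term, or which contrast at which visit, is the test of efficacy.
- **Same section, earlier sentence.** "The continuous variables were compared using" Student's t-test, with a χ² test for categorical variables. The sentence follows the one on descriptive statistics.
- **Sample size {14}.** The planning effect is "the effective amount of JPS joint position perception difference *d* = 0.97". "According to power = 80%, alpha = 0.05, and" that d, "the required sample size *n* = 36 is calculated". Then "Considering the loss of 10% sample size, 40 subjects are required". No visit, outcome scale (final value or change) or between-visit correlation is stated.
- **Trial design {8}.** Participants are "randomly assigned in a 1:1 balanced manner".
- **Abstract, Methods/design.** The baseline assessment takes place before surgery, within the two weeks beforehand, and so before any study training.

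**The concern.** The label and the listed terms do not match. An analysis of covariance adjusts for a covariate, but the list holds only a group factor, a time factor and their product. The time factor is described as running from baseline, so the literal reading makes the pre-surgery value one of the repeated outcomes.

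Two things then follow. First, with three levels of time the treatment × time interaction is an omnibus test on 2 degrees of freedom. By itself it does not estimate the between-arm difference at week 12 or at any other visit, and the plan names no contrast that does. Second, the trial was sized on one standardised difference between two groups. The power of the interaction depends on the correlation between visits and on how the effect builds up from week 6 to week 12, and neither is stated. In a 40-patient trial the choice of term decides whether the planned power is kept, exceeded or missed.

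**Working it through.** **Inputs from the protocol.** d = 0.97, alpha 0.05, power 80%, 36 evaluable patients (18 per arm at 1:1), 10% loss, visits at baseline, week 6 and week 12.

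**Assumptions added here.** Two-sided test; d in units of the standard deviation at a single visit; unit variance at every visit; one common correlation ρ between any two visits; zero expected difference at baseline because of randomisation. Two effect patterns at baseline / week 6 / week 12: 0, d, d (full effect at both visits) and 0, d/2, d (half the effect at week 6).

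**Step 1: the plan's own figure.** For a two-sample t-test the noncentrality is d × √(n/2) = 0.97 × √9 = 2.91. With 34 df the critical value is 2.032 and the power is 80.7%. With 17 per arm it is 78.3%, so 18 per arm (36 in total) is the smallest size that reaches 80%. A one-sided test would need about 14 per arm, so the stated number is two-sided. Allowing for loss, 36 / 0.9 = 40. The stated sample size is reproduced.

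**Step 2: treatment × time with baseline as a level of time.** The noncentrality is λ = (n/2) × S / (1 − ρ), where S is the sum of squared deviations of the three visit effects from their mean. The F test has 2 and 2 × 34 = 68 df, and the critical value is 3.132.

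- Pattern 0, d, d: S = (2/3) × 0.97² = 0.627, so λ = 5.645 / (1 − ρ).
- Pattern 0, d/2, d: S = (1/2) × 0.97² = 0.470, so λ = 4.234 / (1 − ρ).

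**Step 3: week-12 difference with the baseline value as covariate.** Adjustment multiplies the residual variance by 1 − ρ². The noncentrality is 2.91 / √(1 − ρ²) with 33 df. For ρ = 0.5 this is 2.91 / 0.866 = 3.36.

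**Results, 18 per arm.**

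| Test | ρ = 0 | ρ = 0.3 | ρ = 0.5 | ρ = 0.7 |
|---|---|---|---|---|
| Two-group t-test, one visit | 80.7% | 80.7% | 80.7% | 80.7% |
| Interaction, 2 df, effects 0, d, d | 53.7% | 70.1% | 84.6% | 97.4% |
| Interaction, 2 df, effects 0, d/2, d | 42.0% | 56.8% | 72.3% | 91.9% |
| Baseline-adjusted week-12 contrast | 80.6% | 84.2% | 90.3% | 97.7% |

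The interaction reaches 80% at a correlation of about 0.44 under the first pattern and about 0.58 under the second. The adjusted week-12 contrast is above 80% at every correlation tried.

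**The case against.** The strongest reply is that the word ANCOVA itself implies a covariate. The phrase independent variables may mean the factors only, with baseline as an intended but unlisted covariate and weeks 6 and 12 as the repeated measures. The article condenses a fuller document, and covariate lists are often left to an analysis plan. This stands as a possible reading, so it cannot be said that the plan does treat baseline as an outcome visit or ignore it. It does not remove the point: the article lists its terms, baseline is not among them, and the only mention of baseline in that sentence is in the span of the time factor.

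Several stronger readings are tempting but are not supported.

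- **That the trial is underpowered.** The sample size is right for the comparison it assumes, and leaving baseline out of a single-visit comparison still gives 80.7%. The interaction also exceeds 80% at higher correlations.
- **That the treatment main effect, diluted by the baseline visit, is the efficacy test.** With effects 0, d, d it would have 73% / 64% / 56% power at correlations 0.3 / 0.5 / 0.7. But the text ties effectiveness to change over time, which points to the interaction.
- **That each endpoint is given two tests.** The t-test sentence is paired with the χ² test, follows the descriptive statistics and precedes a separate sentence on effectiveness. It may well concern group characteristics only.
- **That patients with a missed visit would be dropped.** No estimation method or complete-case rule is stated, so this cannot be attributed to the plan.

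**Conclusion.** The point holds as a mismatch between the model's label and its listed terms, together with the absence of a named efficacy contrast. It is not an error in the sample size. Power for the 2-df interaction ranges from 57% to 97% over correlations of 0.3 to 0.7 and the two effect patterns, against 84% to 98% for a baseline-adjusted week-12 difference from the same patients. The advantage is large at low correlation (70% or 57% against 84% at 0.3) and almost nil at 0.7 when the full effect is present at both visits (97% against 98%).

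These figures rest on an assumed common correlation, equal variances, two assumed effect patterns and d taken on the single-visit scale. The document gives none of these. If baseline was always meant as a covariate, one clause settles that half of the point, and the primary contrast still has to be named. The matter should be corrected because the better analysis is free, but it does not threaten the validity of the trial.

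**What to change.** Reword {20a} so that:

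1. weeks 6 and 12 are the outcome visits;
2. the baseline value of the outcome is named as a covariate, beside treatment, visit and treatment × visit;
3. one primary contrast is named, for example the adjusted between-arm mean difference at week 12 with its 95% confidence interval.

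A model that uses every available post-baseline visit would fit the intention-to-treat aim stated in {18b} and {20c}. The covariance structure can be left to the statistical analysis plan. It would also help to say whether the t-test and χ² test are for describing the groups only, and to state in {14} which visit and scale d = 0.97 refers to.

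The cost is wording only, made before the outcome data are analysed. The baseline value is already collected, so no new data, visits or patients are needed, and the sample size of 40 can stay.

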**Methods/design:**

This study is a prospective single-center randomized clinical trial to be conducted in the Sports Medicine and Orthopedics of Zhongda Hospital Southeast University. Forty participants aged 18–50, preparing to undergo anterior cruciate ligament reconstruction, and initial anterior cruciate ligament reconstruction using hamstring tendons as grafts will be randomly assigned to the intervention or comparator group. People in the intervention group will add proprioceptive training three times a week, 20 min each time. The intervention will be conducted on the first day after surgery. The researcher mainly collects the data of joint of sense, gait, and plantar pressure. The assessment will be divided into three stages: after signing the informed consent form (within 2 weeks before surgery), 6 weeks after surgery, and 12 weeks after surgery.

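### The effectiveness model is called an ANCOVA but names no covariate and no deciding term, and the 80% power belongs to a two-group comparison at one visit, not to any term of that model

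*Protocol article*

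**What the plan says.** The section on statistical methods for primary and secondary outcomes ({20a}) analyses effectiveness "with change over time (from baseline to week 6 and week 12" and says that "repeated measures analysis of covariance (ANCOVA) will be applied, and treatment, time, and the treatment × time interaction as independent variables". No covariate appears in that list, and no term or visit is singled out as the test of effectiveness. A Student's t-test for continuous variables is also mentioned, without purpose or time point. On reporting, the section says: "The results are reported as mean ± SD and their 95% CIs".

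The abstract (Methods/design) places the assessments "after signing the informed consent form (within 2 weeks before surgery), 6 weeks after surgery, and 12 weeks after surgery". Training begins the day after surgery (Intervention description {11a}), so the first assessment precedes any treatment.

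The sample size section ({14}) takes "the effective amount of JPS joint position perception difference *d* = 0.97" from earlier work. It continues "According to power = 80%, alpha = 0.05" and "the required sample size *n* = 36 is calculated", then "Considering the loss of 10% sample size, 40 subjects are required".

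**The concern.** The label and the listed terms do not agree. An ANCOVA adjusts for a covariate, and the listed model has only arm, time and their interaction. If baseline is a level of time, as the stated span suggests, two candidate tests arise that answer different questions:

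- The treatment main effect averages the arm difference over three visits, one of which precedes treatment and can carry no effect.
- The treatment × time term is a 2-df test of any difference in profile. It is not an arm difference at a named visit.

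The trial was sized for neither. The article does not say which term decides, so the true power is unknown and the choice could be made after the data are seen. The pre-operative measurement could sharpen the comparison at no extra cost, but the text does not put it to its most efficient use. Reporting a mean and SD also does not clearly deliver an adjusted arm difference.

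**Working it through.** **Inputs from the article.** d = 0.97, power 80%, alpha 0.05, n = 36 rising to 40 with 10% loss ({14}); 1:1 allocation ({8}); assessments before surgery and at 6 and 12 weeks (abstract); model terms ({20a}).

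**Assumptions, not in the article.** Equal SDs, the same correlation r between any two visits, no true baseline difference, two-sided tests. The week-6 effect is taken as equal to, or half of, the week-12 effect.

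**1. The plan's own figure.** Two-sample t-test, non-central t, d = 0.97: 17 per arm gives 78.3% and 18 per arm gives 80.7%. So n = 36 reproduces, and 36/0.9 = 40. The calculation contains no repeated measures and no correlation.

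**2. Treatment main effect over three visits.** The mean difference is (0 + 0.97 + 0.97)/3 = 0.647 SD. The SD of a patient's three-visit mean is sqrt((1 + 2r)/3). The standardised effect is therefore:
- r = 0.3: 0.647/0.730 = 0.885
- r = 0.5: 0.647/0.816 = 0.792
- r = 0.7: 0.647/0.894 = 0.723

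It equals 0.97 when sqrt((1 + 2r)/3) = 2/3, that is r = 1/6. Below that value, averaging three visits gains more than the pre-treatment visit costs; at r = 0 power is 90%. Above it, power is lower than for the t-test. Reaching 80% would need 22, 27 and 32 evaluable patients per arm at r = 0.3, 0.5 and 0.7.

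**3. Treatment × time, 2 df.** Non-central F with 2 and 4(18 − 1) = 68 df, and non-centrality (18/2) × S/(1 − r). S is the sum of squared deviations of the visit effects from their mean. With effects (0, 0.97, 0.97), S = 0.627. With (0, 0.485, 0.97), S = 0.470. At r = 0.5 and the full effect, the non-centrality is 9 × 0.627/0.5 = 11.3.

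**4. Baseline-adjusted week-12 difference.** The standardised effect is 0.97/sqrt(1 − r²), on 33 df. At r = 0.5 it is 0.97/0.866 = 1.12.

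**Power at 18 per arm**

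| Test | Week-6 effect | r = 0.3 | r = 0.5 | r = 0.7 |
|---|---|---|---|---|
| Main effect, three visits | full | 73% | 64% | 56% |
| Main effect, three visits | half | 49% | 41% | 35% |
| Treatment × time (2 df) | full | 70% | 85% | 97% |
| Treatment × time (2 df) | half | 57% | 72% | 92% |
| Baseline-adjusted, week 12 | either | 84% | 90% | 98% |

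At r = 0 the adjusted week-12 contrast has 80.6%. With the full effect at both visits, the interaction passes 80% at r of about 0.45 (77% at r = 0.4).

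**5. Change from baseline at week 12**, the other possible reading of the time span. The standardised effect is 0.97/sqrt(2(1 − r)), giving 67%, 81% and 95% at r = 0.3, 0.5 and 0.7. This too misses 80% when the correlation is low.

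**The case against.** The best defence is that this is a condensed article. The word ANCOVA itself implies a covariate, baseline is the obvious candidate, and the listed terms may be only the factors. The levels of time are not listed, and the phrase also fits two change scores. A separate analysis plan could settle all of this. That is why the time-level reading is given here as the natural one and not as a stated fact. What remains is that the article does list the model terms, and they do not match the name it gives the model.

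Second, the 80% does match a test that {20a} mentions, the Student's t-test. But that test has no stated purpose or visit, and the sentence on effectiveness names the repeated-measures model instead.

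Third, a reader might infer that counting baseline as a time point dilutes the treatment effect whatever is tested. The article does not support that. Only the main effect is averaged down, and this costs power relative to the t-test only when r exceeds 1/6 (full effect at both visits). Treatment × time is not diluted. It draws on baseline through the within-patient correlation, and is well powered at moderate to high r with the full effect at both visits.

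A reader might also infer that the estimate is biased. It is not: the contrasts stay unbiased under randomisation, and each candidate test keeps its type I error under the usual assumptions. Keeping baseline in the outcome vector is not wrong in itself either, since a longitudinal model with a common baseline mean is about as efficient as ANCOVA.

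**Conclusion.** The point holds as one of efficiency and of an unspecified deciding test. The sample size arithmetic is correct, but its 80% is attached to an unadjusted two-group comparison at one visit and to no term of the repeated-measures model. Depending on which term decides, on r and on the week-6 effect, power at 18 per arm runs from 35% to 97% over r = 0.3 to 0.7. The baseline-adjusted week-12 contrast stays at 80.6% or above from r = 0 upwards in the cases computed. These ranges rest on an assumed common correlation, equal SDs and two assumed week-6 effects; the article gives none of these. The text should be corrected before analysis. Validity is not at risk, so this is a recommended correction and not a fault that invalidates the plan.

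**What to change.** In {20a}:
- Make the week-6 and week-12 values the outcomes. The model contains arm, visit, arm × visit, the baseline value of the same outcome, and baseline × visit. A longitudinal model constrained to a common baseline mean is an acceptable equivalent.
- Name one arm contrast as decisive. Week 12 is a reasonable choice because it fits the abstract's three-month objective, though the article does not rank the two visits. The other visit is then supportive.
- Report that contrast as an adjusted mean difference with its 95% CI.
- State what the Student's t-test is for.

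In {14}, say that the 80% refers to an unadjusted two-group comparison at one visit and is approximately a floor for the adjusted contrast (80.6% against 80.7% at r = 0, higher as r rises).

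The cost is wording and one or two degrees of freedom. No further patients, visits or data are needed.
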